#### Core Activity 1 study population

2.2.3

To comprehensively examine infant feeding decision making and experiences in the context of HIV in the U.S., it is essential to include the perspectives of multiple participant groups who influence, support, and enact these decisions (Table 2). Approximately 50 WLHIV will participate in a single IDI. These 50 WLHIV will be recruited from 5 sub-groups with approximately 10 individuals in each, including: (1) pregnant women who are considering breastfeeding; (2) pregnant women who are not considering breastfeeding; (3) postpartum women who did not breastfeed for any duration; (4) postpartum women who breastfed for less than 4 weeks and have weaned; (5) postpartum women who breastfed for 4 weeks or longer.

WLHIV participants will each be asked to identify one individual (e.g., partner, family member, or other) who both: 1) is aware of their HIV status; and 2) played an important role in influencing their infant feeding decision (“influential individuals”). It is anticipated that not all WLHIV will be able to identify an influential individual who meets these criteria. Approximately 25 influential individuals will be selected to complete a single IDI. Approximately half of the enrolled influential individuals will be identified by WLHIV who, at the time of enrollment, have breastfed (if postpartum) or intend to breastfeed (if pregnant) and half by WLHIV who do not intend to or did not breastfeed.

Approximately 45 HCPs or AHPs with experience caring for WLHIV and/or their infants will be interviewed. These 45 participants will be recruited from 3 sub-groups of approximately 15 each, including: (1) HCP with experience caring for WLHIV (e.g., midwife, obstetrician, nurse, adult infectious disease specialist, advance practice provider); (2) HCPs with experience caring for infants of WLHIV (e.g., pediatrician, pediatric infectious disease specialist, nurse, advance practice provider); (3) AHPs who are involved in the care of pregnant and postpartum WLHIV and/or their infants (e.g., social worker, lactation support provider, patient navigator, pharmacist, or doula).

The sample sizes for the IDI groups and sub-groups were selected to achieve a maximum variation sample inclusive of the wide geographic and demographic populations of interest and to meet standard qualitative requirements for thematic saturation (i.e., pattern explanation) within groups, while also providing the opportunity for thematic saturation within specific sub-groups and potentially across sub-groups (75–77). While data saturation is not required for the qualitative analysis approach, the planned minimum sample size per stratified group (*n* = 10) fits within the range recommended for descriptive qualitative analyses in homogenous groups (78, 79). Enrollment will be assessed weekly to ensure a sufficiently diverse sample of IDI groups and sub-groups and modifications will be made to ensure diversity and variability. Enrollment will be continuous and close when the target sample is reached.

#### Data collection for IDIs and healthcare professional surveys

2.2.4

All IDIs will be audio-recorded through Zoom with a backup recording using Voice Notes. The audio files will be automatically stored on a secure server at the University of Colorado and subsequently transcribed by an approved AI software (Avidnote), which has strict privacy and data access policies. Transcripts will be stored on the same secure server at the University of Colorado and deleted within Avidnote after transcription. A member of the qualitative team will review each transcript alongside the audio to ensure accuracy and make any needed revisions. Names or other identifying information divulged during the interview will be redacted from the transcripts. Finalized transcripts will be linked to the participant only by their PID. The audio files and transcripts will be password protected. After analysis is complete, de-identified data files (e.g., transcripts and coding frameworks) from qualitative interviews will be stored at Frontier Science's File Exchange Utility (FEU), a secure web-based facility and then processed into the IMPAACT Central Database for long term storage. The audio recording will be deleted (from all servers) after the transcription has been certified as accurate and coding has been completed.

Healthcare professionals will complete self-administered electronic surveys directly in Medidata Patient Cloud using tablets, or in fillable pdf files with the data subsequently entered into Medidata RAVE by site staff.

#### Qualitative analysis

2.2.5

Qualitative data from IDI transcripts will be analyzed using a combined deductive and inductive rapid thematic analysis approach to more efficiently disseminate information to guide decision-making around infant feeding in the context of HIV. Rapid thematic analysis enables researchers to identify relevant themes efficiently and systematically without the long timelines of traditional line-by-line qualitative coding methods. Our rapid thematic analysis approach will use a team to extract insights and key points from the IDIs into matrices to provide easy interpretation of the meanings in the data (80, 81). For each population group (i.e., pregnant women, postpartum women, influential individuals, and HCPs/AHPs), we will create a templated summary table with pre-specified domains (*a priori* deductive codes) based on the interview guides, existing literature, and study objectives, with a column to input key points (inductive) and illustrative quotes for each interview transcript. The table will have the option to input additional inductive domains that may emerge from the IDI transcripts as well. For key points, the team will use short understandable bullets with one data point per bullet to paraphrase and summarize, which are not intended to be interpretative. Verbatim quotes from the interview transcript will be copied to illustrate key points where appropriate and confirmability of data interpretation.

After completion of the summary tables for each transcript, we will consolidate all data by participant type into matrices. Each matrix will have the domains listed as columns, and all transcripts listed in rows. The key points and illustrative quotes from each transcript will be included in each row in the relevant domain. This enables quick review to identify reoccurring and discrepant themes within each domain. The most salient themes and illustrative quotes will then be summarized with affinity maps and other tools during qualitative team meetings, including team members from The Well Project with lived experience, and stakeholder workshops used to establish key findings and conclusions.

To establish calibration, all analysts will complete a summary table for the same single transcript within each group and meet to compare, discuss, and refine. If needed, an additional calibration process and meeting will occur. Once 50% of summary tables are complete for each IDI group, the qualitative team will also hold a calibration check-in meeting to review reoccurring key points and emergent domains, and the potential need to re-calibrate if large discrepancies are observed among the analysts. If re-calibration were to occur, previously coded transcripts would be re-coded in summary tables and reviewed by the team until calibration is achieved.

#### Quantitative analysis

2.2.6

Quantitative data collected from healthcare professional surveys will be analyzed descriptively. Frequencies and percentages for categorical data, and mean, standard deviation, median, Q1 and Q3 for continuous data will be reported as a whole, by site, and by provider type. The individual provider survey responses will be linked to the provider transcripts during final analysis and used to help contextualize themes and interpretations.

#### Landscape analysis

2.2.7

Each participating site will complete site-level surveys in REDCap hosted by Frontier Science. Monthly surveys will collect the total number of WLHIV who deliver and who initiate breastfeeding at each site to estimate site-level prevalence of breastfeeding among WLHIV. We will use baseline and annual site surveys to collect data on site characteristics, current approaches to infant feeding counseling and the clinical management of WLHIV and their infants, and site-determined strengths and challenges in the care of breastfeeding WLHIV. No individual-level data, such as HIV-related laboratory results, will be collected in the landscape surveys. Approaches used to support health and optimize care around infant feeding for WLHIV and their infants will be gathered and compared across sites. Quantitative data collected from site-level surveys will be analyzed descriptively by reporting frequencies of various descriptive measures by site, staffing model, etc. Survey data will also be used to calculate the proportion of postpartum women with HIV within each site and aggregated across sites who breastfeed for any duration, and to create a 95% confidence interval to estimate the proportion of WLHIV who choose to breastfeed. These data will be used to construct a landscape analysis that will provide a broad overview of the trends, emerging issues, and opportunities in supporting infant feeding decision making for U.S. WLHIV. Findings from the repeat site-level surveys will help assess changes in the field as a whole and at the site level across the years of the study.

### Core Activity 2 (CA2)

2.3

#### Core Activity 2 objectives

2.3.1

The primary, secondary, and exploratory objectives of CA2 are presented in Table 3.

**Table 3 T3:** Objectives of Core Activity two.

Objective Type	Objective
Primary	Describe infant feeding practices and identify aspects of clinical, behavioral, and social factors associated with different infant feeding choices and durations among WLHIV
	Identify factors associated with detectable HIV RNA or DNA in breast milk
Secondary	Describe key outcomes among WLHIV according to infant feeding choice
	Describe key outcomes among infants of WLHIV according to infant feeding choice
	Determine the costs and cost-effectiveness of different infant feeding choices
	Identify factors associated with detectable HIV RNA in the plasma of WLHIV who breastfeed
	Describe the temporal relationships between detectable HIV DNA or RNA in breast milk and detectable plasma HIV RNA among WLHIV
Exploratory	Explore risk factors for infant HIV acquisition during breastfeeding

WLHIV, woman living with HIV.

#### Longitudinal cohort

2.3.2

Core Activity 2 will include a prospective observational longitudinal cohort of WLHIV and their liveborn infants (*n* = 450). Approximately half of WLHIV in CA2 will be WLHIV who intend to breastfeed or are breastfeeding at enrollment. Study visits will be conducted at entry and 6 (+/−2), 20 (+/−4), and 48 (+/−4) weeks post-birth for all participants. Breastfeeding WLHIV-infant dyads will complete additional study visits at 7 (+/−7) days post birth, at the time of any breastfeeding complications, and at weaning (Figure 3). Complication visits will be triggered by a plasma viral load of >50 copies/mL for the WLHIV and/or a breast problem, including painful breast swelling, red or shiny skin, cracked or bleeding nipples, blocked ducts, abscess, rash or dermatitis, with or without associated fever. Participants will be instructed to notify site staff immediately when symptoms of a breast problem occur so that a complication visit can be scheduled in a timely fashion. All participants will be followed until infant HIV testing is complete and at least 48 weeks post-birth. Participants who have completed infant HIV testing by 48 weeks post-birth will exit the study at 48 weeks. Breastfeeding participants who have not completed infant HIV testing by 48 weeks post-birth will exit the study at 24 weeks after the infant's last exposure to breast milk, or at 96 weeks post-birth, whichever comes first.

**Figure 3 F3:**
[figure not shown]
Study visits in Core Activity Two. Checkmarks indicate the timing of required study visits for breastfeeding and replacement feeding mother/infant dyads.

#### Core Activity 2 study population

2.3.3

The longitudinal cohort will enroll approximately 450 women with HIV who are ≥28 weeks pregnant or up to 7 days postpartum and their live-born, singleton infants. A cut off of at least 28 weeks’ gestation was selected to reduce enrollment of women who may experience a pregnancy loss and based on literature demonstrating that infant feeding decisions may change early in pregnancy (82).

#### Core Activity 2 data collection

2.3.4

At each study visit, data will be collected, including maternal and infant medical and medication history, infant feeding history, and participant anthropometrics (height and weight for WLHIV; weight, length and head circumference for infants). Additional clinical data and laboratory results will be abstracted from the medical record. Trained research staff at UPLIFT sites will collect clinical and laboratory data and enter it into Medidata Rave.

Self-administered electronic surveys will be completed by WLHIV at each study visit, collecting data on demographic characteristics, socioeconomic status, physical and mental health, and infant feeding intentions and experiences. Survey instruments were adapted from those used in other studies [e.g., the Health Outcomes around Pregnancy and Exposure to HIV/Antiretrovirals (HOPE) study]; sourced from previously published surveys; or developed specifically for UPLIFT (Supplementary Table) (83). Participants will enter survey data directly into Medidata Patient Cloud using tablets during study visits. Research staff will be available to assist as needed. Surveys will be available in multiple languages, either using existing validated non-English versions or via certified translation, and/or can be completed with an interpreter to facilitate enrollment of a diverse cohort of WLHIV.

An IDI will be conducted at the 48-week post-birth visit with approximately 20 postpartum participants who breastfed and approximately 20 participants who never breastfed. These interviews will focus on evolving infant feeding experiences, decision-making over time, and perceived supports and challenges.

#### Breast milk specimen collection

2.3.5

Breast milk samples will be collected at each study visit from breastfeeding participants until weaning is complete. Milk will be expressed from both breasts according to participants’ preferred method, which may include hand-expression or the use of a manual or electric breast pump. A minimum of 15 mL and maximum of 60 mL of breast milk will be collected at most visits, with smaller minimum and maximum volumes allowable in the first 14 days postpartum, when the milk supply is not yet established. Milk will be refrigerated immediately and processed within 6 h of collection. Milk will be centrifuged and the fat layer discarded. The aqueous layer of milk will be aliquoted and cryopreserved. Breast milk cells will be cryopreserved as a nonviable cell pellet. Breast milk samples will be shipped to a centralized laboratory for batched analysis. HIV RNA will be measured in the aqueous milk compartment and HIV DNA will be measured in the breast milk cells using quantitative PCR. Results of breast milk HIV testing will not be shared with sites nor participants, because the assays will not be performed in real time, and the research assays are not approved for clinical use.

#### Case review of breastfeeding-associated infant HIV transmission

2.3.6

Infant HIV acquisition is expected to occur very infrequently, if at all, in the UPLIFT study. In the event that an HIV transmission to a breastfeeding infant is identified during the study, an adaptation of the Fetal & Infant Mortality Review-HIV Prevention Methodology (FIMR-HIV) will be performed (84, 85). The FIMR-HIV process will include a structured maternal interview, collation of medical and medication history for the mother and infant and maternal self-administered survey data collected at study visits (Supplementary Table), and a virtual collaborative case review. Case reviews may include site staff, clinical providers for the mother and infant, select study team members (as applicable), and other relevant individuals such as representatives from the local public health department or patient advocates. Site staff will complete a standardized case review form documenting participant characteristics, a deidentified case summary, proposed recommendations, and an action plan. The goal of FIMR-HIV is to identify and address missed opportunities for prevention of HIV transmission.

#### Core Activity 2 quantitative analysis

2.3.7

In order to describe infant feeding practices and identify aspects of clinical, behavioral, and social factors associated with different infant feeding choices and durations among WLHIV (CA2 co-primary objective), we will describe infant feeding among CA2 participants in several ways. Participants will be categorized by infant feeding method: breastfeeding (defined as receiving breast milk from the mother with HIV for any duration) and replacement feeding (defined as no exposure to breast milk from the mother with HIV). We will report the number and proportion of women who initiate breastfeeding among those who intended to breastfeed, and those who complete their intended duration of breastfeeding.

Several baseline factors will be evaluated as predictor variables to explore factors associated with type of infant feeding. These baseline factors include: geographic location (site); year enrolled; demographic factors (race, ethnicity, age, internationally born, language, marital status); clinical factors (gravity/parity, timing of HIV diagnosis, viral load, CD4 count, ART adherence); social and structural determinants of health (education, employment, income, housing, food insecurity, transportation); healthcare access; health literacy; HIV disclosure; HIV-related stigma; interpersonal violence; substance use; and depression/anxiety symptoms. Three different logistic regression models will be used to identify the statistically significant baseline factors that are associated with the binary outcomes: breastfeeding vs. replacement feeding, exclusive breastfeeding vs. exclusive replacement feeding, and whether a participant completes their intended duration of breastfeeding. Additionally, a generalized linear regression model will be used to determine the baseline factors associated with the continuous outcome, duration of breastfeeding. No adjustments for multiple comparisons are planned. For each model, the marginal regression for each factor will be applied to screen for significant factors first, and then the best subset regression variable selection approach will be used to determine the significant factors in the regression model. For linear regression models, standard diagnostic procedures will be conducted to evaluate key model assumptions, including linearity of covariate effects, normality of residuals, homoscedasticity, independence of observations, and the absence of influential outliers. Linearity will be assessed using various plots and summary diagnostics, and homoscedasticity through residual scatterplots and formal tests when appropriate. For logistic regression models, assumptions will include correct specification of the logit link, linearity of continuous covariates on the log-odds scale, absence of multicollinearity, and lack of overly influential observations; these will be assessed using diagnostic plots, variance inflation factors, and influence measures such as delta-beta statistics. If assumption violations are identified, prespecified corrective actions will be implemented.

Missingness of data will be summarized by groups and key covariates, and graphical and tabular diagnostics will be used to assess whether data are plausibly missing completely at random (MCAR), missing at random (MAR), or missing not at random (MNAR). For the primary analyses, regression models will be fit using methods appropriate to the assumed missingness mechanism, with complete-case analysis applied only when missingness is minimal and unlikely to introduce bias. When missing data are non-negligible, multiple imputation using fully conditional specification will be employed.

We will describe the proportion of milk samples among breastfeeding participants that contain detectable HIV RNA and DNA (co-primary objective). Also, we will use mixed effects logistic regression models to identify statistically significant factors associated with detectable HIV in milk. These will include baseline and other factors including time of sample collection (i.e., study visit); presence of mastitis; presence of nipple trauma; presence of mixed feeding; and presence of plasma viremia in plasma sample collected per standard of care nearest (and within +/- 14 days) to the date of milk sample collection.

We will use logistic and generalized linear regression models to determine whether infant feeding method is associated with maternal mental health and quality of life survey scores, decision regret, satisfaction with infant feeding choice, and infant growth and development, and to identify factors associated with detectable plasma viral load. The temporal relationship between detectable HIV in breast milk and in plasma will also be described (secondary objectives).

Transmission of HIV to infants via breastfeeding is unlikely to occur in this study given the low risk of transmission among WLHIV on ART with sustained viral suppression, the close monitoring and regular follow up of participants in a research study, and the sample size of anticipated breastfeeding WLHIV. We will describe any infant HIV transmissions, including the maternal plasma viral load and presence of detectable HIV in milk, along with additional data gathered from FIMR-HIV review (exploratory objective).

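### The CA2 initiation proportion is not limited to intention recorded before birth, although women already breastfeeding are recruited up to 7 days postpartum; some entry predictors then follow the outcome

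*Protocol article*

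**What the plan says.** - **Who enters.** Section 2.3.3 enrols "women with HIV who are ≥28 weeks pregnant or up to 7 days postpartum", with their infants. Section 2.3.2 adds: "Approximately half of WLHIV in CA2 will be WLHIV who intend to breastfeed or are breastfeeding at enrollment". Women who already have the outcome are therefore an explicit recruitment target.
- **The outcome.** Section 2.3.7 defines breastfeeding as "receiving breast milk from the mother with HIV for any duration". The outcome is met at the first exposure.
- **The initiation proportion.** Section 2.3.7: "We will report the number and proportion of women who initiate breastfeeding among those who intended to breastfeed". No restriction by time of enrolment is given.
- **The models.** Section 2.3.7: "Several baseline factors will be evaluated as predictor variables to explore factors associated with type of infant feeding". Logistic regression is to "identify the statistically significant baseline factors that are associated with the binary outcomes: breastfeeding vs. replacement feeding", and a second model compares exclusive breastfeeding with exclusive replacement feeding. The factors include "clinical factors (gravity/parity, timing of HIV diagnosis, viral load, CD4 count, ART adherence" as well as disclosure, stigma and depression/anxiety symptoms. Site and year of enrolment are listed; antenatal versus postpartum enrolment is not.
- **When data are collected.** Under sections 2.3.2 and 2.3.4, surveys, including those on feeding intentions, are completed at study visits, the first being entry. For a postpartum enrollee, entry is after birth. Laboratory results are abstracted from the medical record.

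**The concern.** There are two linked problems.

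1. **Initiation.** A woman recruited while breastfeeding cannot fail to initiate. If she is counted as an intender, she adds one to both numerator and denominator because of how she was selected. The proportion then no longer describes how often an intention formed in pregnancy is carried out, which is the figure a clinician would want for counselling.
2. **Order in time.** For postpartum enrollees, a survey answer given at entry follows the start of feeding. A factor such as depression or anxiety may then partly reflect feeding and not predict it. The plan allows for this direction itself: later in section 2.3.7, maternal mental health scores are modelled as outcomes of feeding method. If the feeding groups differ in the share enrolled postpartum, the difference between third-trimester and first-week measurement could also create associations on its own.

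**Working it through.** **The plan's own figures first.** Section 2.3.8 takes 450 women, 150 breastfeeding (p = 1/3), 5% loss, 80% power and two-sided α = 0.05.

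- N = 450 × 0.95 = 427.5.
- Continuous factor (Hsieh formula): MDOR = exp[(1.960 + 0.842)/√(N·p(1−p))] = exp[2.802/√95] = 1.333. The plan states 1.34.
- Binary factor with prevalence 0.5, Wald variance of the log odds ratio, event rate 1/3 in the unexposed: 1.749. The plan states 1.75.

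These figures reproduce. The point concerns the denominator and the timing of measurement, not the arithmetic.

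**Bias in the initiation proportion.** Let s be the share of counted intenders who enrolled already breastfeeding, and q the initiation rate among antenatal intenders.

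- Reported proportion = s·1 + (1−s)·q
- Bias = s + (1−s)q − q = s(1−q)

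The article gives neither s nor q, so both are assumptions here:

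| q | s = 10% | s = 20% | s = 30% | s = 50% |
|---|---|---|---|---|
| 60% | 64% | 68% | 72% | 80% |
| 80% | 82% | 84% | 86% | 90% |

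Over this grid the bias runs from 2 points (0.10 × 0.20) to 20 points (0.50 × 0.40).

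**Illustration from the plan's counts.** Half of 450 is about 225 in the group who intend to or already breastfeed. Assume all 150 expected breastfeeders come from that group, which the article does not say. Then 150/225 = 66.7% is already the pooled figure. If k of the 150 enrolled already breastfeeding, antenatal initiation is (150−k)/(225−k):

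- k = 25: 125/200 = 62.5%
- k = 50: 100/175 = 57.1%
- k = 75: 75/150 = 50.0%
- k = 100: 50/125 = 40.0%

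**Which predictors are exposed.**

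- Not exposed: site, year, race, ethnicity, age, birthplace, language, timing of HIV diagnosis, and laboratory values charted before birth.
- Exposed, in postpartum enrollees only: self-reported factors that can change around birth, such as depression/anxiety, stigma, disclosure and adherence.
- Outcomes affected: breastfeeding versus replacement feeding and, in part, exclusivity. Duration and completion of intended duration still lie ahead at day 7, although the intended duration is then stated after birth.

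**Precision if a model is limited to antenatal enrollees** (same formula, p = 1/3, N = 427.5 × (1 − share enrolled postpartum)):

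- 10% postpartum: N = 384.75, MDOR 1.35
- 20%: N = 342, MDOR 1.38
- 30%: N = 299.25, MDOR 1.41
- 50%: N = 213.75, MDOR 1.50

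**The case against.** The strongest reply is that the denominator may already be the right one. Section 2.3.2 names women who intend to breastfeed and women who are breastfeeding as separate groups, and the initiation sentence uses only the language of intention. The authors may mean antenatal intenders only, and the full protocol may say so. This stands to the extent that a reader cannot conclude that the plan does count already-breastfeeding women as intenders. It does not remove the point: the sentence carries no restriction, and entry surveys on intentions are completed by postpartum enrollees too.

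Other parts of the reply also stand:

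- A reader might infer that baseline predictors in general are measured after the outcome. They are not. Many are fixed, and laboratory values may predate birth.
- A reader might take 150/225 as the true antenatal rate and inflate it further, to 70% or more. That would count the already-breastfeeding women twice, because the 225 include them.
- A reader might infer that postpartum women who intended to breastfeed but did not start are missed. The 7-day window is open whatever the feeding method. The narrower criticism is that their earlier intention could only be recalled.
- The initiation proportion is one of several descriptive outputs under a co-primary objective and does not drive the sample size.
- If few women enrol postpartum, or nearly all antenatal intenders initiate, the bias is small. The Discussion's limitations paragraph expects half the cohort to breastfeed, which would point to a high q.

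**Conclusion.** The point holds in a limited form. As written, the initiation proportion can include women who initiated by selection, and any such inclusion pushes it upward by s(1−q). The direction is certain once they are included (for q below 100%); the size is not known. It is 4 to 20 points under the assumed q = 60% and s = 10–50%, and 2 to 10 points at q = 80%. The documents do not establish that these women will be counted, only that nothing in the article excludes them.

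The timing problem is confined to self-reported, time-varying factors in postpartum enrollees, and to the breastfeeding versus replacement feeding model and, in part, the exclusivity model. Leaving enrolment timing off the listed factors means that the models as described cannot separate it from feeding. The analyses of duration and of completion of intended duration are not invalidated.

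**What to change.** 1. Compute the initiation proportion only in women whose intention was recorded before birth. Report postpartum enrollees separately.
2. Include enrolment timing (antenatal versus postpartum) in the breastfeeding versus replacement feeding model and in the exclusivity model, whatever variable selection does with the other factors.
3. For depression/anxiety, stigma, disclosure, adherence and similar self-reported time-varying factors, report the associations in antenatal enrollees, at least as a sensitivity analysis. Use the last viral load and CD4 count before birth.
4. Keep postpartum enrollees in the duration and completion-of-intention analyses, with a flag that their intended duration was stated after birth.

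This changes analysis wording only; recruitment and visits stay as they are. The cost is a smaller denominator for initiation and less precision where a model is limited to antenatal enrollees: a continuous MDOR of 1.35–1.38 instead of 1.33 if 10–20% enrol postpartum, and 1.50 if half do. At that upper end, a sensitivity analysis may be preferable to replacing the main model.
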